#### Physiological Measures

##### Cortisol Awakening Response

Participants take saliva measures themselves on 2 consecutive Fridays of the experiment to measure cortisol levels. A total of 4 samples are taken each week: immediately after awakening, 15 minutes after awakening, 30 minutes after awakening, and 45 minutes after awakening. Participants are instructed not to eat, brush their teeth, smoke, exercise, shower, or drink anything other than water between awakening and taking the final sample to avoid any contamination of the samples or confounding of cortisol values [38]. Saliva is collected using sealed swabs designed for cortisol collection (Salivettes; Sarstedt AG and Co). Cortisol is assessed in saliva with a competitive electrochemiluminescence immunoassay using a Modular Analytics E602 immunoanalyzer (Roche Diagnostics). Cortisol activities are measured and expressed in nmol/L. Participants track the times when they take the saliva measures in a smartphone app, using a phone that they receive from an experimenter and use throughout the study to allow the researchers to verify that they were awake and took the required samples at the correct time. Because cortisol samples remain stable at varying temperatures for up to 5 days [41], participants were not required to cool or freeze the samples once collected. Samples were retrieved by a researcher and frozen on the same day they were collected.

The cortisol measure requires participants to be awake, but the scent conditioning procedure operates for half an hour before the participant wakes. To investigate whether the conditioning procedure has an effect before awakening, heart rate variability and actigraphy measures are included that operate throughout the night. These measures also allow for an additional check for whether the participant did indeed awake at the scheduled time.

##### Heart Rate Variability

Heart rate is measured using Polar H7 and H10 heart rate sensors (Polar Electro Oy) connected to the Heart Rate Variability Logger smartphone app [42] using the same phone as the one required for registering cortisol measures. Participants equip themselves with the heart rate monitor before going to bed on the first Thursday and every day of the second week, so that it stays on throughout the night. On days when they perform the saliva measures, the monitor is kept on until the end of those measures (ie, 45 minutes after awakening) so that any changes in heart rate that accompany the change in cortisol levels during this period can also be measured.

##### Actigraphy

Actigraphy is performed using Motionwatch 8 wearable motion detectors (CamNtech Ltd). Measures are taken over the entire 2-week period with 1-minute epochs.

#### Questionnaires

All questionnaires used have previously been found to have adequate validity and reliability.

For screening, the participants complete the PSQI [40]. Scores of 5 or higher indicate poor sleep and are used as an exclusion criterion. In addition, participants are screened for mental disorders using the MINI-Plus [39,43] and excluded if they meet the criteria for any disorder.

Several personality characteristics are measured upon inclusion, to check for possible interaction with the main outcome. Specifically, the questionnaires used are the extraversion and neuroticism scales of the Eysenck Personality Questionnaire [44,45] to measure extraversion and neuroticism, the Depression Anxiety Stress Scale-21 (DASS-21 [46]) to measure symptoms of depression and anxiety, the Life Orientation Test–Revised [47] to measure optimism, the Perceived Stress Scale [48] to measure general appraisal of stress, and the Morningness-Eveningness Questionnaire [49] to measure chronotype.

Every day of the study, immediately after awakening or after the first saliva measure, participants complete a web-based diary on their phone or PC, which includes several questionnaires. To measure positive and negative affect, the Positive and Negative Affect Schedule (PANAS [50,51]) is used. Stress is measured using a custom-made Numerical Rating Scale (NRS) asking participants to score themselves between 0 (“not at all”) and 100 (“very much”) on 7 stress-related words [19,52]. Vitality is measured using the Subjective Vitality Scale (SVS [53]), and fatigue using the fatigue subscale of the Checklist Individual Strength (CIS [54]) adjusted to measure the current state of fatigue.

The sleep diary also includes custom-made daily questions about habits that indicate or may influence sleep quality and patterns. Participants are asked about their meal times; their intake of caffeine, alcohol, tobacco, medication, and recreational drugs; sporting activities; the time at which they fell asleep the previous night and the time at which they awoke in the morning; any nighttime awakenings; and their perceived sleep quality.

### Procedure

An experimenter screens interested applicants through a telephone interview consisting of questions about relevant exclusion criteria (*Participants* section) and vocal administration of the PSQI (no data are saved). If participants meet the criteria, a follow-up screening session at Leiden University is scheduled to obtain written informed consent, perform a more elaborate check of mental and physical health, and to further explain the procedure and schedule meetings. This screening session consists of several questions about sleep, stress, and health and the Mini-International Neuropsychiatric Interview (MINI) plus international psychiatric interview. Participants who pass the screening also complete the Eysenck Personality Questionnaire – Revised Short Scale, Life Orientation Test–Revised, DASS-21, Perceived Stress Scale, and Morningness-Eveningness Questionnaire in this session. To ensure that the participants know how to take a sample of their saliva, they practice using the swabs used in the study under the supervision of a member of the research team.

The procedure of the actual experiment takes place over a period of 2 weeks, always starting on a Monday and ending on the second Friday. All measurements are performed at the participants’ homes; an experimenter visits the participants at several points to deliver and take equipment, check on participants’ health and stress, offer instructions on study procedures, and check whether all measurements have been completed successfully. Participants indicate their regular time of awakening before the experiment starts and instructed to set their alarm for this time for every day of the study. They are instructed to try to fall back asleep if they wake earlier than the indicated time. However, if they are fully awake, they should start all measurements at the earlier time of awakening.

The measures begin once an experimenter delivers the equipment on Monday of the first week. Participants are checked for exclusion criteria, instructed in the procedure for the coming days, and put on the actograph watch. The (waterproof) actograph watch will be worn continuously until the study ends, barring special circumstances such as high-contact sports or interactions with sensitive equipment where the watch could cause an issue, in which case it can be removed for the duration of the activity. Up until the evening of Thursday of week 1, participants fill in the web-based diary each morning at awakening and indicate their wake and sleep times on the actograph. Thursday evening, they put the heart rate monitor around their chest and wear it for the following night. On Friday morning, when waking up at their regular time of awakening, the first saliva measure is taken. Participants then complete the morning’s sleep diary, followed by another saliva measure 15, 30, and 45 minutes after awakening. An additional diary, where the PANAS, Stress NRS, SVS, and CIS-fatigue are completed again, is taken after the third saliva measure. After the last saliva measure, the participants remove the heart rate monitor. An experimenter arrives later in the day to take saliva measures for analysis.

During the weekend and on the morning of the following Monday, participants only complete the web-based sleep diary and indicate their sleeping times on the actograph. On Monday, an experimenter arrives to install the scent delivery system. This device has been preprogrammed to deliver the distinctive scent 30 minutes before the participant’s regular awakening time. Participants continue to complete the diary and use the actometer in the second week, and starting Monday evening, they also wear the heart rate monitor every night. An experimenter comes by again on Thursday to reset the scent delivery system to go off 4 hours earlier than previously, that is, 4 and a half hours before regular awakening. The experimenter also checks the participant’s experience with the scent device at this time and notes if the participant had any unexpected reactions or has woken up early. Unbeknownst to the participant, if the participant is in the control group, the cartridge containing the scent is also switched for a different cartridge containing a different scent. The participant is instructed to set their alarm 4 hours earlier than normal and perform saliva measures at the new time of awakening and 15, 30, and 45 minutes later. They also use the web-based diary to complete the PANAS, Stress NRS, SVS, and CIS-fatigue directly after the first and third saliva measures. After the final saliva measure, the participants are allowed to return to sleep. They awake at a time of their choosing the following morning and only at that point remove the heart rate monitor. Their only remaining activity that day is a final diary filled in at a time of the participant’s choosing. Later that day, an experimenter picks up the saliva samples and all equipment, including the actometer that the participant can at that point remove, and debriefs the participant about the true aim of the study and their group assignment.

### Data Management

Self-reported data will be entered electronically by participants and checked for completion throughout the study at each experimenter visit. These data will be stored on a secure server that produces daily backups. Saliva samples are stored securely in a freezer at Leiden University Medical Center until study completion. All data are handled in compliance with the Leiden University Data Management Policy (available at request). Personal data are kept separate from the research data, and the file connecting the 2 is secured and only accessible to the study staff. Owing to low risk, external monitoring was deemed unnecessary by the ethical review committee, but a department data manager will monitor the data during the study and check the data package for completeness at study completion. Data will be stored locally for a period of 15 years after study completion and will be uploaded to the Data Archiving and Networked Services database to be accessed at request.

### Statistical Analysis

The data will be checked for outliers and all relevant assumptions. If cortisol values deviate strongly from normality, a log transformation will be performed. An α level of .05 will be used for all analyses, and an effect size (Cohen *d* or partial eta squared, as appropriate) will be calculated for all effects.

Sensitivity analyses will be performed to investigate the effect of including participants who do not show a CAR in week 1 (defined as an increase of at least 2.5 nmol/L above baseline [8]) and the effect of including participants with incomplete data.

A conditioned effect on cortisol values can be defined in 2 ways: by a higher increase in the CAR from baseline (first week) to evocation (second week) for the experimental group (same scent on evocation) than the control group (different scent on evocation), and by a higher increase in the initial cortisol value (first measure of the CAR) from baseline (first week) to evocation (second week) in the experimental group than in the control group. Therefore, 2 separate analyses will be performed. For the first definition, cortisol levels over each day will be transformed into a single score by computing the area under the curve with respect to the first value (area under the curve with respect to increase [7]). We will then perform a linear mixed-model analysis with week (baseline vs evocation) and group (experimental vs control) as fixed factors. For the second definition, we will again perform a linear mixed-model analysis, replacing the area under the curve with respect to increase value with the first cortisol value after awakening. To check for confounding variables, sociodemographic and personality variables will be included as random factors in both the analyses.

Linear mixed models are also used to analyze the secondary outcomes. Heart rate variability measures 30 minutes before awakening and 45 minutes after awakening will be analyzed separately. In both cases, week (baseline vs evocation) and group will again be fixed factors. For the secondary psychological outcomes affect, stress, vitality, and fatigue, the measurement time (0 vs 30 minutes after awakening) is added as an additional fixed factor.

Finally, multivariate regression will be used to explore the possible moderating or mediating role of psychological variables (affect, personality, and perceived stress) on the effects of conditioning.

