## Discussion

The design of this study is intended to classically condition the CAR by repeatedly presenting a scent in the half hour immediately before awakening, immediately before the CAR normally occurs. If the conditioning is successful, participants should respond to the CS with higher cortisol levels even when it appears in the middle of the night, when cortisol levels are normally far below the morning levels. The outcomes of this study could offer more insight into learning during sleep, learning influences on physiological processes, and manipulating the diurnal rhythm. These findings may also aid in the treatment of sleep rhythm and cortisol disorders.

This study uses a novel design that combines the finding that conditioning is possible during sleep [24,25] with the idea that the diurnal rhythm itself could be conditioned [31,32]. While other studies have investigated whether cortisol levels are subject to classical conditioning [19,21-23], all of them have used an external UCS to adjust cortisol levels rather than relying on changes brought upon by the natural diurnal rhythm. Even animal studies that relied on less invasive stimuli kept the animals under artificial lighting conditions that are impossible to replicate in daily human life [31,32]. Should the alternative approach of this study be successful in conditioning the CAR, this could indicate that it is not necessary to rely on medication or highly demanding procedures to influence cortisol levels.

Should the conditioning procedure used in this study be successful in affecting subjective wakefulness measures, then a similar conditioning procedure has potential use in the treatment of sleep disorders. The primary target group would likely be those patients who do not respond to or cannot participate in existing behavioral therapies. Pharmacological therapies currently prescribed for this purpose are not always ideal solutions; many, such as benzodiazepines, do more to deregulate than help the sleep cycle and feature unpleasant side effects and risks of dependence [55].

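### A check on the distribution of cortisol values can decide whether the primary AUCi measures an absolute or a relative rise, and the group contrast can then change sign

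*Protocol article*

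**What the plan says.** The Abstract names the cortisol awakening response (CAR) as the primary outcome, measured in saliva at 0, 15, 30 and 45 minutes after waking. The Statistical Analysis section begins with a general undertaking to look for outliers and check assumptions. It then sets a conditional rule: "If cortisol values deviate strongly from normality, a log transformation will be performed". It gives no criterion for a strong deviation and does not name the stage at which the log is applied.

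The section then defines a conditioned effect in two ways.

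- **CAR:** success is shown "by a higher increase in the CAR from baseline (first week) to evocation (second week) for the experimental group" than for the control group. Each day's samples become one score by "computing the area under the curve with respect to the first value", that is, AUCi.
- **First sample:** the same contrast is applied to the first sample alone, replacing AUCi "with the first cortisol value after awakening".

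Both outcomes go into a linear mixed model with week and group. The section does not say whether the increase in the CAR is meant as an absolute or a proportional one.

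**The concern.** For many outcomes a log is a harmless way to deal with skewness. AUCi is different because it is built from differences from the first sample. Differences of logs are log ratios, so logging the samples changes what AUCi measures. The rule therefore lets a feature of the observed data choose between two questions for the primary outcome: did cortisol rise by more nmol/L, or by a larger factor?

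The trigger is also aimed at the wrong quantity. The normality assumption of a linear mixed model concerns its residuals, here those of AUCi, and not the distribution of cortisol values as such.

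What is at stake is the direction of the primary result. The two scales part company when the first sample is raised, and a raised first sample is what the second definition predicts in the experimental group.

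**Working it through.** The plan gives no figure to reproduce: it states no concentrations, standard deviations or power calculation. The check is algebra, followed by an illustration with assumed values.

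**Formula.** With samples S1 to S4 at 0, 15, 30 and 45 minutes (Cortisol Awakening Response section), the trapezoid area above the first sample is

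AUCi = 15 x (S1/2 + S2 + S3 + S4/2) - 45 x S1 = 15 x [(S2 - S1) + (S3 - S1) + (S4 - S1)/2].

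On raw values this depends only on differences from S1. With ln S in place of S, each term becomes ln(Sj/S1), so it depends only on ratios to S1.

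**When the signs differ.** Take equal week 1 profiles in both groups and a control test-night profile that rises after S1. Let the experimental profile have first sample k x S1 and increments m x (Sj - S1).

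- Raw: experimental AUCi = m x control AUCi, so the contrast is positive when m > 1.
- Log: each ratio is 1 + (m/k) x (Sj/S1 - 1), so the contrast is positive only when m > k.

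The signs are opposite whenever 1 < m < k. This needs no particular concentrations, and the base of the log does not matter.

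**Illustration (all concentrations assumed, nmol/L).** Week 1 is 10, 13, 15, 14 in both groups. The control test night is 4, 5.5, 6.5, 6.

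- Control, raw: 15 x (1.5 + 2.5 + 1.0) = 75.
- Control, log: 15 x [ln(1.375) + ln(1.625) + ln(1.5)/2] = 15.10.
- Experimental 6, 7.8, 9, 8.4 (k = 1.5, m = 1.2), raw: 15 x (1.8 + 3.0 + 1.2) = 90.
- Experimental, log: 15 x [ln(1.3) + ln(1.5) + ln(1.4)/2] = 12.54.

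The contrasts are 90 - 75 = +15.0 and 12.54 - 15.10 = -2.56. Other cases from the same control profile:

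| k | m | Raw contrast | Log contrast |
|---|---|---|---|
| 1.125 | 1.05 | +3.75 | -0.83 |
| 1.5 | 1.2 | +15.0 | -2.56 |
| 2 | 1.2 | +15.0 | -5.31 |
| 1.5 | 1.5 (all samples scaled) | +37.5 | 0 |
| 1.5 | 1 (2 nmol/L added throughout) | 0 | -4.37 |
| 1 | 1.2 | +15.0 | +2.39 |

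The first three rows reverse. The next two make one contrast zero. The last, with equal first samples, agrees in sign.

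The week effect in the control group flips too. From week 1 to the test night, raw AUCi falls from 150 to 75 while log AUCi rises from 12.54 to 15.10. The Discussion expects this kind of drop in level, since testing takes place "when cortisol levels are normally far below the morning levels".

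**Logging AUCi itself.** With the control test-night means, lognormal values, a between-person coefficient of variation (CV) of about 0.5 and a within-person CV of about 0.2 (all assumed), about 4% of simulated AUCi values were negative. A log of AUCi is therefore not generally usable.

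**Sampling variation.** The simulation used 21 per arm (the 42 completers, equal split assumed), between-person CVs of 0.3, 0.5 and 0.7, within-person CV 0.2, and 2,000 runs per setting. For k = 1.5, m = 1.2, the raw and log estimates had opposite signs in 0.408 to 0.425 of trials. With no effect the figure was 0.161 to 0.262.

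**The case against.** The strongest reply is that the article does not state the details on which harm would depend. It names no normality test, does not say that samples are pooled over times and weeks, and promises a check of assumptions that could include residuals. It also uses the term cortisol values when introducing both outcomes, so the check might be meant at the level of AUCi. The order of log and AUCi may be set out in a fuller document. Much of this stands: nobody can say from the article that the log will be triggered. A reader might infer that a check on mixed morning and night samples is bound to fail, but the text does not describe such a check. What remains is that the rule as printed ties a log to the observed distribution, and neither way of applying it to AUCi works without cost. Logging first changes the meaning, and logging afterwards fails at zero or below.

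Second, a residual check would not remove the problem by itself. In the simulations a Shapiro-Wilk test at .05 on the residuals of raw AUCi change rejected in 21% to 74% of trials. That stands, and it is why the scale must be fixed whatever the check shows.

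Third, reversal is conditional, and some disagreement in sign is noise, as the no-effect figures show. In a further simulation, both scales were significant in opposite directions in at most 0.05% of runs. This limits the claim: two contradictory significant results are not a realistic prospect. The log analysis alone was significantly negative in about 10% of runs for the k = 1.5, m = 1.2 profile, so the scale still affects interpretation.

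Fourth, the first-sample analysis tests a raised first sample directly. That is so, but it does not settle what AUCi reports in the same situation.

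Two further inferences are tempting and unsupported. The study is single-blinded and experimenters swap the control cartridge, but the article does not say who makes the scale decision or whether that person sees group labels. And the week 1 responder criterion, "defined as an increase of at least 2.5 nmol/L above baseline", is a classification for a sensitivity analysis. Keeping it in raw units while modelling logs is not a contradiction.

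**Conclusion.** The point holds in a limited form. The conditional log rule can change the primary AUCi from an absolute to a relative rise, and the plan does not say which is intended. The sign condition 1 < m < k is exact for profiles in which the increments share one multiplier, week 1 is equal between groups and control cortisol rises after waking. The sizes (+15.0 against -2.56, and the simulated proportions) rest on assumed concentrations and CVs. Logging before forming AUCi is an inference, though the only generally workable order. A reader might conclude that a log would reverse the result; the documents support only that it could, in a situation that the second definition makes plausible.

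**What to change.** State before the analysis that the primary AUCi is computed from untransformed nmol/L. Check normality on the mixed-model residuals, preferably with group labels masked. If they are clearly non-normal, keep the scale and use bootstrap or permutation inference. Report AUCi of logged samples only as a sensitivity analysis, labelled as a relative increase. For the separate first-sample outcome a log is well defined and may be used, but its scale should also be fixed in advance.

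The Results section reports data collection closed and the analysis not yet complete, so this may still be settled in advance. The cost is a few sentences, one extra analysis and some loss of efficiency if AUCi proves strongly skewed.

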**Methods:**

The study protocol takes 2 weeks and is performed from the participant’s home. Measures in week 1 are taken to reflect the CAR and waking under baseline conditions. For the first 3 nights of week 2, participants are exposed to a scent from 30 minutes before awakening until their normal time of awakening to allow the scent to become associated with the CAR. On the final night, participants are forced to wake 4 hours earlier, when cortisol levels are normally low, and either the same (conditioned group) or a different (control group) scent is presented half an hour before this new time. This allows us to test whether cortisol levels are higher after the same scent is presented. The primary outcome is the CAR, assessed by saliva cortisol levels, 0, 15, 30, and 45 minutes after awakening. The secondary outcomes are heart rate variability, actigraphy measures taken during sleep, and self-reported mood after awakening. To perform manipulations and measurements, this study uses wearable devices, 2 smartphone apps, web-based questionnaires, and a programmed scent device.

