### Design

The study design is summarized in Figure 2. Participants follow a 2-week protocol, with all measurements taking place in their own homes. The first week functions as a baseline measure. In the second week, the scent conditioning takes place on Tuesday through Thursday morning. Participants are exposed to a scent half an hour before awakening, with the aim of conditioning the scent to the CAR. The 30-minute interval was chosen to match the CAR in length and to increase the chance that the participant is still asleep for the length of the scent presentation, while still clearly preceding the CAR and minimizing the time between CS and CAR. It is presupposed that the CAR naturally functions as an unconditioned response to daylight and other zeitgebers that set the diurnal rhythm that serves as the UCS. The final night of the study functions as the test phase. To test whether conditioning has taken place, participants in the experimental group are asked to set their alarm 4 hours earlier than normal, and the scent device releases the trained scent half an hour before this time. This way, the CS is present, while the UCS is not. Participants in the control group wake up at the same time, but for them, the scent has surreptitiously been replaced the previous day with a different, novel scent, so that neither the CS nor the UCS is present. We expect that in the experimental group, the scent (CS) will evoke the CAR and lead to an increase in cortisol levels. While the process of awakening may lead to an increase in cortisol levels in both groups, the presence of the CS would cause this increase to be more pronounced in the experimental group.

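### Two unranked cortisol analyses, each at .05, bear on one primary question, and no rule says how they combine; if either suffices, the error is about 8–10%, not 5%

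*Protocol article*

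**What the plan says.** The abstract (Methods) declares one primary outcome: "The primary outcome is the CAR, assessed by saliva cortisol levels, 0, 15, 30, and 45 minutes after awakening". It does not say which summary of the four samples carries the test.

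The Statistical Analysis section says "A conditioned effect on cortisol values can be defined in 2 ways". Both definitions compare the change from week 1 to week 2 between the groups.

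- **First definition.** The samples of each day are reduced to one score by "computing the area under the curve with respect to the first value", that is, AUCi.
- **Second definition.** The same mixed model is run again, "replacing the area under the curve with respect to increase value with the first cortisol value after awakening".

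The link between them is "Therefore, 2 separate analyses will be performed". The same section states "An α level of .05 will be used for all analyses". The article gives no order of testing, no division of alpha, no requirement that both analyses succeed, and no reading for the case where they disagree. The Design section gives the expected direction: "the presence of the CS would cause this increase to be more pronounced in the experimental group".

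**The concern.** The plan has one primary question, whether cortisol was conditioned, and two tests that each meet a stated definition of yes. Without a decision rule, a positive result on one could be reported as conditioning even if the other is null or points the other way. The error rate of that overall claim would then exceed the .05 that the article states.

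Disagreement between the two is realistic. AUCi is measured from the first sample, so a higher first sample tends to lower it. The scent starts half an hour before awakening, and the section on the CAR measurement allows that conditioning may act before the participant wakes. Such an effect could raise the first sample and flatten AUCi on the same morning.

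The Discussion attributes mixed results in this field partly to confounds and chance in small samples, and hopes to avoid those issues. An uncontrolled second route to a positive claim works against that aim.

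**Working it through.** The article gives no power or family-wise error calculation, so there is no figure of its own to reproduce.

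**Inputs from the article.** α = .05 per analysis and two cortisol analyses (Statistical Analysis); sampling at 0, 15, 30 and 45 minutes (abstract); 42 completers (Participants, Results).

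**Assumptions.** Two-sided tests (sidedness is not stated); equal arms, so 21 per arm among completers (the ratio is not stated); correlation r between the two test statistics (not documented, so a range is shown).

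**1. Independent tests.** Chance of at least one false positive = 1 − (1 − .05)² = 1 − 0.9025 = 0.0975, which is 1.95 times .05. The upper bound for any correlation is .05 + .05 = 0.10.

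**2. Likely sign and size of r.** By the trapezoid rule, AUCi = 15 × (S₁/2 + S₂ + S₃ + S₄/2) − 45 × S₁. The weights on the four samples are therefore −37.5, 15, 15 and 7.5. They sum to zero, and their squares sum to 1406.25 + 225 + 225 + 56.25 = 1912.5. With equal variances and a common within-day correlation c,

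corr(S₁, AUCi) = −37.5 × √(1 − c) / √1912.5 = −0.857 × √(1 − c).

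For c = 0.3, 0.5, 0.7 and 0.8 this gives −0.72, −0.61, −0.47 and −0.38. If the correlation instead decays with the time between samples (first-order autoregressive), the values are −0.77, −0.68, −0.55 and −0.46. If the same structure carries over to the week-to-week change, r lies roughly between −0.4 and −0.8.

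**3. Correlated tests.** From the bivariate normal with limits ±1.96:

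| r | Any two-sided rejection | False claim in the hypothesised direction |
|---|---|---|
| 0 | 0.0975 | 0.0494 |
| −0.3 | 0.0951 | 0.0499 |
| −0.5 | 0.0907 | 0.0500 |
| −0.7 | 0.0835 | 0.0500 |
| −0.8 | 0.0781 | 0.0500 |

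Over the likely range of r, the two-sided error is about 8–9%, or 1.6 to 1.9 times .05. The directional error, which is 0.025 for a single two-sided test, almost exactly doubles at zero or negative correlation. If the tests were one-sided at .05, it would go from 0.05 to 0.0975–0.10.

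**4. Check by simulation.** Two t tests on change scores with 21 per arm gave a two-sided error of 0.095 at r = 0, 0.091 at −0.5 and 0.083 at −0.7.

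**5. After a correction.** With .025 for each test, the error is 1 − 0.975² = 0.0494 if independent and 0.0465 at r = −0.5.

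**6. Cost.** The detectable standardised difference at 80% power with 21 per arm (noncentral t, 40 degrees of freedom) is 0.886 at .05 and 0.983 at .025. The normal approximation, √(2/21) × (z for α/2 + 0.842), gives 0.865 and 0.951.

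**The case against.** Four points on the other side deserve weight.

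- **No either-or rule is written.** A reader might infer that the plan declares success on either analysis. That is the natural reading of two alternative definitions, but the article does not say it. If both analyses had to succeed, the error would not be inflated. What the text supports is that the rule is missing; the 8–10% is conditional on the either-or reading.
- **Correction is not forbidden.** A reader might also infer that a single α of .05 for all analyses excludes any adjustment. The sentence does not mention multiplicity and can be read as a nominal level. A correction method could stand in a fuller document that is not shown. Even so, the article itself sets two definitions of the primary effect beside one stated level and does not order them, and that needs resolving.
- **The first sample is a reasoned target.** It is tempting to say that it is not part of the CAR. The abstract includes the 0-minute sample in the primary outcome, and the Statistical Analysis section treats it as the first measure of the CAR. A rise before waking is also plausible under this design. So a raised first sample with a lower AUCi is not necessarily a contradiction, which is why the plan needs a stated reading for it.
- **The study is exploratory.** The Participants section calls the design novel and exploratory, describes a pilot and reports no power analysis. This lowers the stakes. It does not remove them, because the Discussion links a positive result to managing without medication and to treating sleep disorders.

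A family-wise figure for the secondary outcomes would add little. Those outcomes lie outside the primary claim, and independence is implausible for mood, stress, vitality and fatigue scored in the same diary.

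**Conclusion.** The point holds in conditional form. The article fixes one primary outcome but two unranked analyses of it, each at .05, with no hierarchy, alpha split or rule for discordant results. If a positive result on either is read as conditioning, the two-sided family-wise error is 9.75% for uncorrelated tests and about 8–9% under the negative correlation that the construction of AUCi makes likely. A doubling of the two-sided error is therefore the upper end, not the expected value. The directional error does nearly double, from 2.5% to 4.9–5.0%.

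These figures rest on two-sided tests and an assumed correlation. Given the exploratory, pilot character of the study, this should be fixed rather than treated as disqualifying.

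**What to change.** Settle the following in writing before the analysis is completed. The Results section says data collection is closed and the results are still to come, so a dated change made before the results are seen remains credible.

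1. **Choose one structure.**
   - Preferred: name AUCi, the measure of the increase, as the single primary test at two-sided .05. Test the first sample next, at .05, only if AUCi is significant, or report it as a key secondary outcome.
   - Alternative: keep both as co-primary with Holm, the smaller p-value against .025 and, if that is met, the larger against .05.
2. **State how discordant results will be read,** in particular a raised first sample with an unchanged or lower AUCi.
3. **Limit the α sentence.** Apply .05 to the primary question after this control, and label the secondary outcomes exploratory.

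No new endpoint is needed. Introducing another cortisol summary after data collection closed would raise a post hoc question of its own.

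Cost: wording only. With the fixed order, AUCi loses no power, but the first sample cannot be claimed formally unless AUCi succeeds. With Holm, the detectable d at 80% power rises from about 0.89 to at most 0.98, assuming 21 per arm.
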